### Randomization and blinding

Randomization will be done using permuted blocks (to conceal allocation) and will be stratified by district. The randomization sequence will be developed and controlled by an individual not otherwise involved in the study to ensure fidelity and supervised by co-author HX. After baseline assessment, communes will be randomly assigned to the three sequences (Table 1) in a 1:1:1 allocation ratio stratified by district in variable block sizes implemented in SAS v9.4 to prevent anticipated allocation of the communes to the treatment sequences.

Full blinding of participants will not be possible due to the nature of the intervention.

### Statistical analysis

In preliminary analysis, the distributional aspects of the variables under consideration will be examined through descriptive statistics. These will include measures of location (mean, median, quartiles) and measures of dispersion (range, standard deviation, variance) for continuous variables, and frequencies of the levels of categorical variables. These measures will also assist with a data cleaning/screening procedure to eliminate any possible copying, handling, recording or measurement errors.

The general approach for analyzing all the types of outcomes arising from the study will be the Generalized Linear Mixed-effect Models (GLMM) for longitudinal and clustered measures, with the commune as the clustering variable. These models were used in the previous study [25] and can handle a wide range of types of outcomes including normal, binary, ordinal, and Poisson outcomes, and can account for the correlations for observations within the same clusters. Specifically, the primary endpoint (depression caseness based on PHQ-9) is a binary outcome and will be analyzed using random-effect logistic model, a special case of GLMM. The main independent variables in statistical model specifications will include indicator variables for visits (for secular trend), indicators for VMood intervention effects at months 3 and 6, and district (to control for trial initiation time) and baseline score as fixed effects. Additionally, these models included random effects for communes (the clusters) and for participants nested within communes to account for random variation between communes and between participants within the same commune. By properly setting up the GLMMs, a wide range of scientific hypotheses can be tested, including the primary ones regarding treatment effect estimation. The quality of statistical inferences will be substantiated through rigorous model checking and validation techniques. Data will be analyzed using the PROC MIXED, PROC GLIMMIX and/or PROC NLMIXED in SAS 9.4 software [47]. Subgroup analysis will be performed using the GLMM on the subsets of data formed by the subgroup.

When applying the above statistical models in practice, a potentially important issue is dealing with missing values, which is common in most studies. One advantage of employing the above GLMM is that it uses all the available data by including those study units with missing outcome values and produces valid inference under the assumption of missing at random, which is a more relaxed assumption of missing data mechanism than missing completely at random. The missing values will be regarded as missing at random when the nonresponse behavior is believed to be a function of observed data. The potential bias of these inferences will be quantified if these missing data were suspected to be nonrandom even after conditioning on the observed data using the selection models [48,49].

Another relevant issue is to properly account for treatment adherence (app usage) when evaluating the effect of VMood intervention. Two well-established and complementary evaluation methods will be used to evaluate the impact of the intervention accounting for treatment nonadherence: Intention-to-treat (ITT) and Complier Average Causal Effect (CACE). The primary approach is to apply the method of ITT to estimate causal effects of the assignment to treatment on the trial outcomes for all participants. The ITT has the merit of making use of randomization in RCT. Although ITT analysis is valid, one limitation of ITT analysis is that it estimates the program effectiveness rather than the method effectiveness. The program effectiveness depends on the proportion of compliers, which can change (e.g., when the public change their willingness to take the intervention after they learn the intervention works). Thus, CACE will be applied as a secondary analysis. The CACE analysis estimates causal effects of the assignment to treatment on the trial outcomes for the subgroup of compliers [47,50]. Thus, CACE analysis will complement the above ITT analysis to paint a more complete picture about the impact of treatment on groups of populations that would be of interest to individual patients.

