### Sample size and power calculation

The power calculation assumes that each commune would recruit an average of 8 participants and retain 7 participants after attrition and that the proportion of depression caseness (defined as PHQ-9 score between 10–19) in the control group is 42%, the same as in the previous study [25]. The calculation shows that for a type I error rate of 0.05, and an intracluster correlation coefficient (ICC) of 0.01 (based on data from the previous study on the binary outcome of having depression), a total of 336 participants recruited from 48 clusters (i.e., communes) have at least 80% power to detect treatment differences when the proportion of depression caseness in the intervention group is ≤ 30% (Table 4 below) [46]. The power calculation was performed using Stata 17 [46].

**Table 4 pone.0290328.t004:** Power analysis.

Proportion of depression caseness in Intervention Condition	Power
0.30	81%
0.31	74%
0.32	66%
0.33	57%
0.34	48%

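### Subgroup analysis is fixed as separate model fits in each subset, which gives no test of whether the VMood effect differs between subgroups

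*Protocol article*

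**What the plan says.** The Statistical analysis section gives one sentence on subgroups: "Subgroup analysis will be performed using the GLMM on the subsets of data formed by the subgroup". The primary model is a random-effect logistic model with visit indicators and "indicators for VMood intervention effects at months 3 and 6, and district (to control for trial initiation time) and baseline score as fixed effects", plus random effects for communes and for participants within communes. No subgroup-by-treatment term is listed and no heterogeneity test is mentioned. The remark that these models can test many hypotheses is general and does not refer to effect modification. No subgroup variable is named, and the study objectives contain no subgroup hypothesis.

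The sample size section assumes that "each commune would recruit an average of 8 participants and retain 7 participants after attrition". It states that "a total of 336 participants recruited from 48 clusters (i.e., communes) have at least 80% power" when caseness is 42% under control and at most 30% under VMood, "for a type I error rate of 0.05, and an intracluster correlation coefficient (ICC) of 0.01".

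**The concern.** The question a subgroup analysis answers is whether the effect differs between groups. Separate fits do not estimate or test that difference. With no interaction estimate in the plan, the comparison left to a reader is between the subset results themselves, and the usual form of it is significant here, not significant there. When the whole trial has about 80% power, each subset has far less, so that pattern is common even when the effect is identical in both.

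The trial is meant to inform scale-up across diverse Vietnamese provinces. A false impression that VMood works in one group and not in another could misdirect that decision.

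**Working it through.** **Inputs from the article.** 48 communes; "communes will be randomly assigned to the three sequences (Table 1) in a 1:1:1 allocation ratio stratified by district", hence 16 per sequence; 7 retained participants per commune (48 × 7 = 336); control caseness 0.42; VMood caseness 0.30; ICC 0.01; type I error 0.05, taken as two-sided because that reproduces the table. **Assumed, because the article names no subgroups:** two subsets split 50/50 to 80/20 within communes.

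**Step 1: reproduce Table 4.** Use the Hussey–Hughes variance for a stepped wedge with I = 48 communes, T = 4 periods and m = 7 per commune-period. The total variance is 0.42 × 0.58 = 0.2436, so τ² = 0.01 × 0.2436 = 0.002436 and σ² = 0.99 × 0.2436 / 7 = 0.03445. With treatment indicators X:

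- U = ΣX = 16 × (3 + 2 + 1) = 96
- W = sum of squared period totals = 16² + 32² + 48² = 3584
- V = sum of squared commune totals = 16 × (9 + 4 + 1) = 224

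Var = Iσ²(σ² + Tτ²) / [(IU − W)σ² + (U² + ITU − TW − IV)τ²] = 0.07309 / (1024 × 0.03445 + 2560 × 0.002436) = 0.07309 / 41.51 = 0.001760, so SE = 0.0420.

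Power = Φ(difference / SE − 1.96). For caseness of 0.30 to 0.34 this gives 81.6, 74.6, 66.4, 57.3 and 47.9%, against the stated 81, 74, 66, 57 and 48%. A parallel two-arm calculation (168 per arm, design effect 1.06) gives only 60.6% at 0.30, so the stepped-wedge formula is the one that fits.

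**Step 2: separate fits, same true effect in both subsets.** Set the noncentrality of the full trial to z(0.975) + z(0.81) = 1.960 + 0.878 = 2.838 and scale it by the square root of each subset's share. With subset powers a and b, treated as independent, P(exactly one significant) = a(1 − b) + b(1 − a).

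| Split | Power, larger subset | Power, smaller subset | Exactly one significant |
|---|---|---|---|
| 50/50 | 52% | 52% | 50% |
| 60/40 | 59% | 43% | 51% |
| 70/30 | 66% | 34% | 55% |
| 80/20 | 72% | 24% | 61% |

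Putting m = 3.5 directly into the Step 1 formula gives SE = 0.0582, power Φ(0.12 / 0.0582 − 1.96) = 54% per subset and the same 50% discordance.

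**Step 3: how far this depends on the effect.** If overall power is 48% (VMood caseness 0.34), the range is 40 to 43%. If VMood has no effect at all, it is 2 × 0.05 × 0.95 = 9.5%.

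**Step 4: the interaction test.** With a uniform effect, a valid test rejects 5% of the time. A simplified two-arm simulation with 82 per arm per subset gave 5.0%, while the separate fits were discordant in 46% of runs. For power, the SE of the difference between two subset effects in a 50/50 split is about twice the overall SE. An interaction as large as the overall effect therefore has noncentrality 2.838 / 2 = 1.419 and power Φ(1.419 − 1.960) = 29%. At 80/20 it is Φ(2.838 × √(0.8 × 0.2) − 1.960) = Φ(−0.825), about 20%.

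**Step 5: what the interaction model must contain.** In a stepped wedge, treatment is partly confounded with time. Consider an interaction model with a common secular trend, no effect modification, and subgroup trends diverging by an assumed 5 points per visit. The check used linear GLS with 3 sequences of 16 communes, 3.5 participants per subgroup per commune, ICC 0.01 and participant correlation 0 to 0.5. The month-3 interaction test falsely rejects 7 to 17% of the time if baseline is only a covariate, and 17 to 37% if baseline is also an outcome row. With subgroup-by-visit terms added, it returns to 5%.

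**The case against.** The strongest reply is that this is one sentence in a condensed article about a secondary analysis. A reader might infer that the plan will judge effect modification by comparing subset p-values. The document does not say so, and it makes no subgroup claim. Subset estimates are a legitimate description, and an unseen analysis plan may hold a heterogeneity test. This stands in part: the harm arises only if the subset results are read against each other. It does not remove the point, because the article names the method rather than leaving it open, and the method named cannot answer the subgroup question.

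The size is also conditional. The 50 to 61% needs a real effect of 12 points in both subsets and an assumed split. That is correct, and the smaller figures belong beside it.

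A reader might also infer that the subset fits would be numerically unstable, with thin or empty communes. The documents do not support that claim. No subgroup is named, a subgroup defined by province or district would not thin the communes at all, and a commune without members of a subset does not invalidate a mixed model. No calculation here shows instability, so it is not part of this point.

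Last, separate fits have one merit: each subset gets its own secular trend. A careless interaction model would lose it, as Step 5 shows. That objection stands and shapes the fix.

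**Conclusion.** The point holds as a weakness of a stated method that should be corrected; it is not a threat to the primary conclusion. Separate fits provide no test of effect modification. Under the trial's planning figures and a uniform true effect, exactly one of two subsets would be significant about 50 to 61% of the time, against 5% for a valid interaction test. The figure falls to 40 to 43% if VMood caseness is 34%, and to 9.5% if there is no effect.

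These figures rest on assumed splits and on independence of the two subsets. Independence is approximate because the subsets share communes, but this matters little at an ICC of 0.01. They also rest on the single-effect formula that reproduces Table 4, which is simpler than the planned model. The stronger reading, that the trial will declare subgroup differences from such contrasts, goes beyond the text.

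**What to change.** Replace the subgroup sentence by:

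*Subgroup effects will be assessed in the full data set by adding to the primary GLMM the subgroup, its interactions with the visit indicators, and its interactions with the VMood month-3 and month-6 indicators. The interaction estimates with 95% CIs and p-values, and subgroup-specific estimates with 95% CIs from this model, will be reported as exploratory.*

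The visit interactions keep a separate secular trend for each subgroup. Both VMood indicators are kept because the primary model has both. Subset fits may remain as descriptive support.

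The cost is a few extra terms with the same data and the same SAS procedures. The drawback is low power, about 29% for an interaction as large as the overall effect in an even split and less in uneven ones. The text should state this, so that a non-significant interaction is not read as evidence of equal effects.

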### Economic evaluation

The economic analysis will determine the cost-effectiveness of the Vmood app intervention compared to the control condition (enhanced treatment as usual). Following best-practice recommendations of the Second Panel on Cost Effectiveness in Health and Medicine [51] and for the conduct of cost-effectiveness analysis alongside RCTs [52,53], (i) a trial-based cost-effectiveness analysis (CEA), generated exclusively with trial data; and (ii) a probabilistic model-based CEA, required to capture both the long-term costs and benefits of the intervention will be executed.

As per recommended guidelines for the conduct of CEA alongside RCTs, health resource use and health-related quality of life measures will be obtained directly from trial participants [52,53]. All costs will be estimated from trial data [40] including direct costs attributable to health resource utilization [40], intervention delivery and implementation [54], and indirect costs attributable to productivity impairment [41,42]. Costs will be reported by trial arm as cost per participant enrolled on an intent-to-treat basis. The number of QALYs accumulated during the study period will be estimated from patient reported outcomes collected from trial participants. Model development for capturing the long-term costs and benefits of the intervention will follow best practice recommendations for conceptualizing a model [55] and will be informed by systematic reviews [56] as well as recommendations for modelling the cost-effectiveness of interventions to treat depression [20].

Results will be reported as an incremental cost-effectiveness ratio (ICER) in US$/QALY and VND/QALY at prevailing exchange rates, both from a health-care sector perspective (which will exclude productivity costs) and from a societal perspective, using a 3% annual discount rate for costs and QALYs [51]. Cost-effectiveness will be evaluated at willingness-to-pay thresholds based on per capita gross domestic product (GDP), the approach recommended by the World Health Organization [57]. Uncertainty around ICERs will be quantified with 95% confidence intervals using non-parametric bootstrapping in the trial-based CEA, a method specific to applications with patient-level cost and health outcome data) [58] and cost-effectiveness acceptability curves. Finally, the reporting of the economic analysis will adhere to health economic evaluation reporting standards [59].

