### Overall study design

The study will use a cluster stepped-wedge randomized controlled trial (RCT) design, with three stepped-wedges. Cluster stepped-wedge designs are pragmatic and appropriate for balancing scientific rigour with real world conditions, including the logistic and time constraints often faced by policy makers and health systems [29]. Stepped-wedge designs also represent an ethical approach in circumstances where access to evidence-based interventions is limited because they allow all participants to access the intervention as all clusters cross from the control into the intervention group [29].

In this study, randomization will occur at the commune level and communes will be assigned to receive either the VMood intervention or the control condition first. Participants in communes assigned to the control condition will be provided access to the VMood app and screening and assessment measures, but content will be limited to a video presenting general information about depression. In a typical stepped-wedge design, when a cluster crosses over from control to intervention, they remain in the intervention arm until the study is complete. In this case the intervention period will last three months in accordance with the VMood protocol. We will also collect follow-up data from each cluster three months after they have completed the intervention. Table 1 illustrates the timing of the intervention and control groups in the stepped-wedge design for one study district. Due to the size of the study, which will include 8 districts and 48 communes in total, all communes in the same district will begin the study at the same time but the entry of provinces will be staggered. The study has not started recruiting participants.

**Table 1 pone.0290328.t001:** VMood stepped wedge design by month—one district.

		1	2	3	4	5	6	7	8	9	10	11	12									
C1																						
C2																						
C3																						
C4																						
C5																						
C6																						
		Baseline																				
		Intervention																				
		Control																				
		Follow-up																				
	C	Commune																				

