#### Secondary outcomes

Secondary outcome measures will contribute to study findings across several categories, including clinical, quality of life, economic, and usability. Other clinical outcomes include changes in PHQ-9 and GAD-7 score from baseline to post-intervention. The effect of the intervention on quality of life, including dimensions such as social relationships, perceived well-being, and overall health [34], will be measured using the WHO Quality of Life- Brief (WHOQOL-BREF) [35]. Changes in use of alcohol and tobacco products during intervention use will be measured using the Fast Alcohol Screening Test (FAST) [36] and the Alcohol, Smoking and Substance Involvement Screening Test (ASSIST) [37] adapted to assess tobacco use only. We will also collect data on any other care for depression that participants in both the intervention and control group receive during the course of the study from the HEA.

For the cost-effectiveness analysis (details are presented below), we will estimate health-related quality of life using the EQ-5D-5L [38]. The EQ-5D-5L instrument is available in Vietnamese and has been validated in Vietnam, with country-specific weights based on social preferences obtained from a nationally representative sample available for the calculation of QALYs [39]. Costs attributable to health resource utilization will be estimated from self-reported inpatient and outpatient visits using the Health Economic Assessment (HEA) [40] adapted for the Vietnamese health system context. Indirect costs attributable to potential productivity gains will be measured using the validated Work Productivity and Activity Impairment Questionnaire: Depression (WPAID:D) [41,42].

Finally, the System Usability Scale (SUS) [43] will be used to assess the usability of the VMood app. Participants will complete the full suite of outcome measures at baseline (aside from the SUS), every three months until completing the intervention and at three months after completing the intervention (follow-up). The full suite of outcomes measures will be delivered online using REDCap electronic data capture tools hosted at the Institute of Population, Health and Development (PHAD) in Vietnam [44,45]. See Table 3 for a summary of the full suite of measures.

**Table 3 pone.0290328.t003:** Outcome measures.

Measure	Outcome	Frequency

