** *Economic Outcomes–Cost Effectiveness Analysis* **		
EQ-5D-5L	Functioning; can use this to calculate QALYs	Baseline, and at every 3 months until 3 months post-intervention
HEA–adapted	Costs attributable to health resource utilization	Baseline, and at every 3 months until 3 months post-intervention
WPAID:D	Indirect costs attributable to potential productivity gains	Baseline, and at every 3 months until 3 months post-intervention

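### The planned bootstrap 95% confidence interval on the trial-based ICER loses its meaning if about 2.5% or more of replicates show no QALY gain; net monetary benefit from the same replicates avoids this

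*Protocol article*

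**What the plan says.** The Economic evaluation section of the protocol article reports results as an ICER in US$ and VND per QALY, from a health-care sector and a societal perspective, and judges it against thresholds tied to per capita GDP. On uncertainty it says: "Uncertainty around ICERs will be quantified with 95% confidence intervals using non-parametric bootstrapping in the trial-based CEA". The same sentence adds "and cost-effectiveness acceptability curves".

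The horizon of this analysis is the trial itself: "The number of QALYs accumulated during the study period will be estimated from patient reported outcomes collected from trial participants". Utilities come from the EQ-5D-5L, and Table 3 sets its timing as "Baseline, and at every 3 months until 3 months post-intervention". Under Overall study design, "the intervention period will last three months in accordance with the VMood protocol". Measured benefit therefore runs for about six months from the start of the intervention. Longer-term effects go to a separate analysis, "a probabilistic model-based CEA, required to capture both the long-term costs and benefits of the intervention".

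The article gives no expected QALY gain, utility SD, cost difference or standard error. It also gives no rule for replicates whose QALY difference is zero or negative, and it mentions neither net monetary benefit nor the cost-effectiveness plane.

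**The concern.** The ICER divides a cost difference by a QALY difference. As the denominator passes through zero, the ratio jumps from plus to minus infinity. On either side of that jump, equal values can mean opposite things. A negative ratio arises when the intervention costs less and does more, and also when it costs more and does less. Sorting such values and reading off limits does not produce a range of plausible cost-effectiveness.

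A weakly determined denominator is plausible here. The horizon is short, and the trial is sized for a binary caseness outcome rather than for utility. From the societal perspective productivity savings enter the numerator, so the cost difference may change sign as well.

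Cost-effectiveness is one of the trial's two stated aims and is meant to inform scale-up. Readers will use an interval printed beside the ICER.

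**Working it through.** **1. The plan's own figure.** Table 4 gives 81% power for caseness of 42% against 30%. I used the Hussey-Hughes stepped-wedge variance with three sequences of 16 communes, four periods, 7 participants per commune per period, ICC 0.01, variance 0.42 × 0.58 and two-sided alpha 0.05. For 0.30 to 0.34 this gives 81.2, 74.2, 66.0, 56.9 and 47.5%, against the stated 81, 74, 66, 57 and 48%. The table reproduces. The implied SE of the caseness difference is 0.0422, so z = 0.12 / 0.0422 = 2.85 at the design effect.

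**2. What a crossing does to the interval.** This is an illustration with independent normal replicates and a cost difference of 3 SE. Ratios are in units of cost SE over QALY SE.

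| QALY z | Point ratio | Replicates ≤ 0 | 2.5th to 97.5th percentile |
|---|---|---|---|
| 1.2 | 2.5 | 11% | about -21 to +25 |
| 1.6 | 1.9 | 5.5% | about -10 to +16 |
| 2.0 | 1.5 | 2.3% | about 0.1 to 9.2 |
| 2.8 | 1.1 | 0.3% | about 0.3 to 3.7 |

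The break comes where about 2.5% of replicates cross zero, near z = 2.

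**3. How likely a crossing is.**

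From the protocol:
- The caseness difference is 0.42 - 0.30 = 0.12.
- There are 336 participants in three sequences, or 112 each.
- The design effect is 1 + (7 - 1) × 0.01 = 1.06.

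Assumed, because the protocol does not give them:
- The utility gap g between cases and non-cases is 0.1 to 0.3.
- The utility SD s is 0.15 to 0.25.
- The baseline correlation r is 0 to 0.5.
- All benefit acts through caseness.
- Sequences start three months apart. At month 3 one sequence is compared with two (information 112 × 2/3). At month 6 the second is compared with the third (112 × 1/2).

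Formulas, with T the years of benefit:
- Gain = 0.12 × g × T.
- SE = s × T × √(1.06 / (112 × (2/3 + 1/2))) × √(1 - r²) = s × T × 0.0901 × √(1 - r²).
- z = 0.12 g / (0.0901 s √(1 - r²)). T cancels, so the choice between 3 and 6 months does not matter.
- Expected share of replicates at or below zero = Φ(-z).
- Chance that at least 2.5% of replicates are at or below zero = Φ(1.96 - z).

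| g | s | r | z | Share ≤ 0 | Chance of ≥ 2.5% |
|---|---|---|---|---|---|
| 0.10 | 0.25 | 0 | 0.53 | 30% | 92% |
| 0.20 | 0.20 | 0 | 1.33 | 9% | 73% |
| 0.20 | 0.20 | 0.5 | 1.54 | 6% | 66% |
| 0.20 | 0.15 | 0 | 1.78 | 4% | 57% |
| 0.20 | 0.15 | 0.5 | 2.05 | 2% | 46% |
| 0.30 | 0.15 | 0 | 2.66 | 0.4% | 24% |
| 0.30 | 0.15 | 0.5 | 3.08 | 0.1% | 13% |

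On a grid of g in steps of 0.05, s of 0.15, 0.20 and 0.25, and r of 0 and 0.5, the chance exceeds one half in 23 of 30 combinations. It drops below one half once g/s exceeds 1.96 × 0.0901 / 0.12 = 1.47 without baseline adjustment, or 1.47 × √0.75 = 1.27 with r = 0.5.

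**4. Cross-check on the stepped-wedge precision of step 1.** The caseness effect in SD units is 0.12 / √(0.42 × 0.58) = 0.243, with z = 2.85. Scaling z in proportion, standardised utility effects of 0.06, 0.12, 0.18 and 0.25 give z of 0.7, 1.4, 2.1 and 2.9. The chances of a material crossing are 90, 71, 44 and 17%, the same pattern as in step 3.

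**The case against.** The strongest reply is that the likelihood comes from inputs the protocol does not contain, and that the simple calculation leans one way. Participants enter with PHQ-9 scores of 10 to 19. Sending all benefit through the cut-off at 10 counts a fall from 18 to 11 as no gain. The protocol's general modelling approach also adjusts for baseline score, which sharpens the estimate. Both points stand. Baseline adjustment is in the range above, while benefit short of the cut-off would raise z further. A reader might infer that the interval will certainly or almost certainly be uninterpretable. The documents do not support that, and at the favourable end the interval is readable.

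It can also be said that the acceptability curves already deal with the problem. They do stay interpretable whichever quadrants the replicates occupy, and a separate long-term model is planned. A reader might infer that the ratio interval is the main or only uncertainty measure. It is not: the sentence lists interval and curves together and ranks neither. The interval would still be printed, however, and the curves do not give it a meaning.

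A reader might further infer that individual patients will be resampled although communes are randomised. The text does not say so. Its reference to patient-level information describes the data the method needs. The resampling unit and the way the limits are formed are details an article may leave to a fuller economic plan, so their absence is not an error. What remains is a method the article does commit to: a confidence interval on the ratio.

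**Conclusion.** The point holds conditionally. An interval formed on the ICER cannot be read in order if about 2.5% or more of replicates have a QALY difference at or below zero. The protocol's figures do not settle whether this will happen. Under the stated assumptions the chance is about 13% to 92%, and above one half for most of the range. The lower figure needs a large utility gap, a small SD and useful baseline adjustment together.

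This is a poor choice of summary, not a contradiction, and it leaves the clinical analysis and the acceptability curves untouched. It is worth correcting because the risk is foreseeable, it bears on one of the two aims, and the remedy is nearly free.

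**What to change.** Report the trial-based ICER as a point estimate. From the same bootstrap replicates, report:
- incremental net monetary benefit (threshold × QALY difference - cost difference) with a 95% CI at each planned GDP-based threshold, for both perspectives;
- 95% CIs for incremental cost and for incremental QALYs separately;
- the acceptability curves already planned.

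Net monetary benefit is linear in both differences, so its interval stays valid wherever the replicates fall. When the text is revised, it would help to say that communes are the resampling unit. That would match the randomisation and the commune effects in the Statistical analysis section.

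The cost is one or two sentences and no new data or replicates. The small downside is that no interval appears on the ratio itself.
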